### **5.5.2 Pre-Cisternal Puncture Procedures**

Patients will undergo standard of care medical evaluations in preparation for cisternal puncture, including anesthesiologist consultation. The neurosurgeon/interventional radiologist and anesthesiologist will review Screening clinical laboratory analyses (including documented negative pregnancy test), brain MRI and MRA, and local ECG results. Medical history and currently prescribed and over-the-counter medications will be reviewed with regards to any recent changes. At the anesthesiologist's discretion, additional clinical assessments may be performed (specific to concomitant medical conditions).

### **5.5.3 Intracisternal Injection**

On Day 0, PR006A will be administered as a single dose via suboccipital injection into the cisterna magna by an interventional radiologist or neurosurgeon. Prior to injection, a volume of intracisternal fluid equivalent to the PR006A dosing volume will be removed. The procedure will be performed under general anesthesia or deep sedation and using imaging guidance in accordance with the Procedure Manual. Patients will remain under observation for 24 hours (overnight inpatient stay) after PR006A administration.

### **5.5.4 Investigational Product Accountability**

The Investigator or designee is responsible for:

1. Logging receipt of each shipment of investigational product,
2. Confirming the actual shipment contents,
3. Verifying receipt of the investigational product by signing the appropriate documentation provided by the Sponsor or its designee, and
4. Indicating the status of each vial.

Accountability will be recorded on the appropriate eCRF. Where permitted, all investigational product will be kept on site until permission is granted by the Sponsor to destroy or return the investigational product. In the event hospital pharmacy requirements will not allow used investigational product vials to be retained for accountability, the site must maintain proper documentation to support accountability for all used investigational product vials no longer present at the site.

The Investigator will maintain accurate records of receipt of all investigational product, including dates of receipt. In addition, accurate records will be kept regarding when and how much investigational product is administered for each patient in the study. Reasons for departure from the expected administration regimen must also be recorded. At the completion of the study, to satisfy regulatory requirements regarding drug accountability and requirements of the Sponsor, all investigational product will be reconciled and returned or destroyed in accordance with written instructions of the Sponsor or according to local hospital pharmacy requirements.

### **5.5.5 Other Supplies**

Ancillary supplies required for dosing will be provided to the investigational sites. Supplies will include syringes, needles, a tubing set, flush buffer formulation, and Omnipaque 240.

### **5.5.6 Overdose Management**

An overdose is any dose of study treatment given to a subject or taken by a subject that exceeds the dose described in the protocol. Overdoses with corresponding clinical signs, symptoms or clinical sequelae should be captured on relevant AE/SAE sections in the eCRF within 24 hours of the site becoming aware of the overdose. Overdoses without signs or

symptoms do not need to be recorded as AEs but should be reported on the relevant sections in the eCRF within 24 hours of the site becoming aware of the overdose.

### **5.5.7 Product Quality Complaint**

A product complaint is any written, electronic, or verbal expression of dissatisfaction regarding the identity, quality, reliability, safety, purity, potency, effectiveness or performance (applicable for approved marketed products) of a drug product after it is released for distribution.

In the course of conduct of the study, study personnel may become aware of a product complaint associated with the use of the investigational product. Study site personnel shall notify Prevail within 24 hours by forwarding the product complaint information via the contact information listed in the Pharmacy Manual. Where possible, personnel should segregate and retain any product, materials, or packaging associated with the product complaint until further instruction is provided by Prevail.

## **5.6 Treatment Compliance**

Treatment compliance will be ensured by an interventional radiologist or neurosurgeon who administers the dose. The success and/or completeness of investigational product administration will be documented by the proceduralist and recorded by the study site personnel in the eCRF.

## **5.7 Prior and Concomitant Therapy**

### **5.7.1 Excluded Medications and/or Procedures**

The following medications and procedures are not allowed during this study:

- Other gene therapy or cell therapy.
- Use of any other investigational drug, devices, stem cells, or experimental therapy.
- Immunization 4 weeks prior to and during Screening, e.g., influenza, tetanus.

Note: Pneumococcal vaccine and shingles vaccine administration is allowed during the Screening Period for patients without documented vaccination coverage within 10 years prior. Patients not previously vaccinated should receive pneumococcal and/or shingles vaccine administration at least 4 weeks prior to sirolimus loading dose.

- Use of antiplatelet therapies and blood thinners at least 7 days prior to and at least 48 hours after intracisternal injection and LPs.
- Patients are encouraged to follow all routinely scheduled immunizations as recommended by their local center for disease control and prevention, including seasonal vaccinations. Consideration should be given to adjusting of the vaccination schedule to avoid vaccination during the period of immunosuppressant administration ([Section 5.5.1](#)). Additionally, the administration of live vaccines is prohibited from 4 weeks prior to sirolimus loading dose and until sirolimus is discontinued.
- The following medications and procedures are not allowed during the period of sirolimus administration:
  - Use of strong inhibitors of CYP 3A4 or P-glycoprotein, including but not limited to bromocriptine, cimetidine, cisapride, clotrimazole, danazol, diltiazem, fluconazole, protease inhibitors (e.g., HIV and hepatitis C that include drugs such as ritonavir, indinavir, boceprevir, and telaprevir), metoclopramide, nifedipine, troleandomycin, and verapamil.
  - Use of strong inducers of CYP 3A4 or P-glycoprotein, including but not limited to carbamazepine, phenobarbital, phenytoin, rifampin, and St. John's Wort

### 5.7.2 Restricted Medications and/or Procedures

Prophylactic use of antiplatelet therapies and blood thinners should be temporarily stopped for at least 7 days prior to and at least 48 hours after intracisternal injection and LPs. Use of strong inducers and inhibitors of CYP3A4/P-gp, including grapefruit juice and over the counter medications (e.g., St. John's wort) is prohibited at least 7 days prior to and at least 48 hours after sirolimus administration.

It is the intent of this protocol to maintain baseline FTD medications unchanged from baseline through the 12-month visit. However, medically necessary changes are permitted, but the reason for dose change must be documented on the appropriate eCRF. Study-specific assessments (safety and efficacy scales) should be performed prior to initiation or change in dose of symptomatic FTD medications.

Any FTD therapy will be collected via eCRF.

### **5.7.3 Documentation of Prior and Concomitant Medication Use**

Use of all concomitant medications will be recorded in the patient's eCRF. The minimum requirement is that drug name and the dates of administration are to be recorded. This will include all prescription drugs, herbal products, vitamins, minerals, and over-the-counter medications. Any changes in concomitant medications also will be recorded in the patient's eCRF.

Any concomitant medication deemed necessary for the welfare of the patient during the study may be given at the discretion of the Investigator. However, it is the responsibility of the Investigator to ensure that details regarding the medication are recorded in full in the eCRF.

## **6 Study Assessments and Procedures**

Before performing any study procedures, all potential patients and their study partners will sign ICFs for overall study participation. Consent for the patient and the study partner are not required to be obtained on the same day; however, consent must be obtained from each patient and their study partner before entering the study.

Patients willing to provide blood and CSF samples for future biomedical research will be required to sign an optional additional section of the main ICF.

Patients and their study partners will have the opportunity to have any questions answered before signing the ICFs. The Investigator must address all questions raised by the patient and/or study partner. The Investigator or designee will also sign the ICFs.

The schedules of activities by visit for this study are presented in [Table 13-1](#) (main study period) and [Table 13-2](#) (follow-up period). The recommended (though not required) sequence of study assessments is provided in [Section 13.2](#). Although the staging and sequence of study assessments is recommended, it will not be a protocol deviation if these assessments are performed in a different order.

Detailed instructions for the conduct of study assessments and procedures will be provided in the Investigator's study manuals.

### **6.1 Efficacy Assessments**

Secondary and exploratory efficacy assessments will also include use of the tools described in the ensuing sections. These include scales evaluating language, behavior, executive functions, and memory.

All patients will undergo longitudinal vMRI assessments to monitor downstream effect of PGRN-associated neurodegeneration on cortical thickness, and white matter lesions will be quantified.

#### **6.1.1 CDR Plus NACC FTLD**

The CDR has been widely used in Alzheimer therapeutic studies. It serves as both a functional assessment instrument and a global rating. The CDR plus NACC FTLD was developed in 2008 as a supplement to the CDR ([Knopman et al 2008](#)). It was designed to

assess the clinical status of patients across the FTLT spectrum of disorders. To capture key FTLT patient characteristics, the CDR plus NACC FTLT adds 2 domains to the CDR: 1) the Behavior, Comportment, and Personality domain; and 2) the Language domain. To complete the CDR plus NACC FTLT, both the study partner and the patient are interviewed using the same CDR semi-structured interview. The following method is used for calculating the CDR plus NACC FTLT in this study: CDR plus NACC FTLT SB is reached by adding each of the 8 domain scores together to yield a single score that ranges from 0 (no impairment) to 24 (severe impairment) ([Miyagawa et al 2019](#)). A CDR plus NACC FTLT global score will also be calculated as per the established method ([Miyagawa et al 2020](#)).

### 6.1.2 Montreal Cognitive Assessment

The MoCA is a rapid screening instrument (similar to the Mini-Mental State Examination). It was developed to be more sensitive to patients presenting with mild cognitive dysfunction. The MoCA assesses 8 domains: attention and concentration, executive functions, short-term and working memory, language, visuospatial abilities, conceptual thinking, calculations, and orientation ([Nasreddine et al 2005](#)).

### 6.1.3 Benson Complex Figure Copy and Recall

Benson Complex Figure copy and recall is intended to assess a patient's visuoconstructional and visual memory functions. It involves the patient copying and recalling the Benson figure:

[figure not shown]

Accuracy and placement are each scored 0, 1, or 2 for the outer rectangle and for the peripheral elements, by the rater, usually a neuropsychologist. The scores are summed, and the lower the total score, the more impaired the patient is considered.

#### **6.1.4 Clinical Global Impressions – Severity/Improvement**

The CGI scale is a psychiatric rating instrument used to assess an Investigator’s opinion of a patient’s psychiatric functioning both before (CGI-S) and after (CGI-I) treatment with an investigational drug. Both the CGI-S and the CGI-I are single-item assessments ([Busner and Targum 2007](#)).

#### **6.1.5 Trail Making Test, Part A and Part B**

Both TMT-A and TMT-B consist of 25 circles distributed over a sheet of paper. In TMT-A, the circles are numbered 1 to 25, and the patient should draw lines to connect the numbers in ascending order. In TMT-B, the circles include both numbers (1 to 13) and letters (A to L); as in TMT-A, the patient draws lines to connect the circles in an ascending pattern, but with the added task of alternating between the numbers and letters (i.e., 1-A-2-B-3-C, etc.). The patient will be instructed to connect the circles as quickly as possible, without lifting the pen or pencil from the paper. The patient is timed as he or she connects the “trail.” If the patient makes an error, this will be pointed out immediately and the patient allowed to correct it. Errors affect the patient’s score only in that the correction of errors is included in the completion time for the task. The text should not be continued if the patient has not completed both parts after 5 minutes have elapsed. Results for both TMT-A and TMT-B are reported as the number of seconds required to complete the task; therefore, higher scores reveal greater impairment.

- For Trail A: Average is 29 seconds, deficient is >78 seconds, “rule of thumb” is most in 90 seconds.
- For Trail B: Average is 75 seconds, deficient is >273 seconds, “rule of thumb” is most in 3 minutes.

#### **6.1.6 Digit Span Test (Forwards and Backwards)**

The Digit Span Test (forwards and backwards) is a very short screening tool that evaluates the patient’s cognitive status. It is administered by the Investigator or designee to quickly evaluate whether a patient’s cognitive abilities are normal or impaired. Administering the test forwards assesses both attention and short-term memory; the backwards version of the test measures working memory.

The patient listens to the Investigator or designee saying a series of numbers and is asked to repeat them in the same order forwards and backwards. The first series is 3 numbers, such as “3, 9, 2.” Each number is said in a monotone voice, 1 second apart. The patient should repeat those numbers forwards and backwards. The second series is 4 numbers, such as, “4, 7, 3, 1.” Again, the patient should repeat those numbers forwards and backwards. The Investigator or designee should continue in the same manner by increasing the series of numbers to 5 and asking the patient to repeat the numbers forwards and backwards.

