**Efficacy Assessments:**

The efficacy of PR006A will be evaluated by changes in the following:

- PGRN levels in blood and CSF
- CDR plus NACC FTLD
- NfL levels in blood and CSF
- Montreal Cognitive Assessment (MoCA)
- Benson Complex Figure Copy and Recall
- Clinical Global Impressions – Severity/Improvement (CGI-S/I) scale
- Trail Making Test, Part A (TMT-A) and Part B (TMT-B)
- Digit Span Test (forwards and backwards)
- Category Fluency
- Multilingual Naming Test (MINT)
- [REDACTED]
- [REDACTED]

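### Digit Span as described in Protocol 6.1.6 uses only 3, 4 and 5 digits and the same digits in both directions, which narrows its range and blurs the backward score (minor)

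*Protocol*

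**What the plan says.** Protocol 6.1.6 sets out the administration in three steps: "The first series is 3 numbers, such as" an example, "The second series is 4 numbers, such as" a further example, and then the rater is told to "continue in the same manner by increasing the series of numbers to 5 and asking the patient to repeat the numbers forwards and backwards". No series shorter than 3 or longer than 5 is mentioned. There is no second trial at a given length, no discontinuation rule and no scoring rule.

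On direction, the section says of the 3-digit series: "The patient should repeat those numbers forwards and backwards". It gives the 4-digit series the same instruction. The general instruction is that the patient "is asked to repeat them in the same order forwards and backwards", which contradicts itself, because digits repeated in reverse are not in the same order.

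On purpose, it says: "Administering the test forwards assesses both attention and short-term memory; the backwards version of the test measures working memory".

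The test is on the efficacy assessment list in the Synopsis. Tables 13-1 and 13-2 schedule it at Screening, Months 6 and 12, and every 6 months from Month 18 to Month 60. Section 6 says that detailed instructions for assessments will be in the study manuals.

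**The concern.** A measure repeated over 5 years to show change needs room to move in both directions. A ladder with three rungs has little. A patient who repeats 5 digits at Screening cannot be seen to improve, and a fall from 7 to 5 looks like no change. A patient who cannot manage 3 digits backwards cannot be seen to get worse. Both ends could matter here, because section 4.1.1 admits patients with a CDR plus NACC FTLD sum of boxes from 1 to 15, on a scale that section 6.1.1 gives as 0 to 24.

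Separately, if the patient has just heard a list and said it forwards, reversing that list is partly a rehearsed task. The backward score then overlaps with the forward one, although the section assigns the two to different functions.

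The trial has no control group and plans 5 patients per cohort, so lost sensitivity in a measure cannot be offset by comparison with another arm.

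**Working it through.** **Step 1. What can be recorded.** The inputs are the series lengths 3, 4 and 5 (Protocol 6.1.6). The protocol defines no score, so I assume that the score is the longest series repeated correctly.

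| True span | Recorded |
|---|---|
| 0, 1, 2 | fails the 3-digit series |
| 3 | 3 |
| 4 | 4 |
| 5, 6, 7, 8, 9 | 5 |

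Between two visits at which the patient passes at least the 3-digit series, the largest recordable change is 5 - 3 = 2 digits. If the score were instead a count of correct series, it would also be bounded, at 3 per direction.

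**Step 2. How much change is lost (illustration only).** The protocol gives no figure to reproduce. Assume a forward span that is normal with SD 1.2 and mean m from 5 to 6.5, rounded to whole digits, with a failure of the 3-digit series counted as one step below 3. Suppose that every patient truly loses 1 digit. The loss is recorded only if the starting span is 3, 4 or 5, so

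recorded mean change = -[Φ((5.5 - m)/1.2) - Φ((2.5 - m)/1.2)].

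The share with a recorded 5 at the start is 1 - Φ((4.5 - m)/1.2). The share whose one-digit loss is hidden by the cap (span 6 or more) is 1 - Φ((5.5 - m)/1.2).

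| Mean m | Recorded 5 at start | Loss hidden by cap | Recorded mean change (true -1) |
|---|---|---|---|
| 5 | 66% | 34% | -(0.66 - 0.02) = -0.64 |
| 5.5 | 80% | 50% | -(0.50 - 0.01) = -0.49 |
| 6 | 89% | 66% | -(0.34 - 0.00) = -0.34 |
| 6.5 | 95% | 80% | -(0.20 - 0.00) = -0.20 |

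With SD 1.0 to 1.5 instead, the share with a span above 5 is 31% to 37% at mean 5 and 63% to 69% at mean 6, so the picture does not hinge on the SD.

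**Step 3. The lower end, backwards.** With the same SD, the share below 3 is Φ((2.5 - m)/1.2): 34% at mean 3 and 11% at mean 4. These patients could not be told apart from one another or seen to decline.

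**Step 4. The two directions.** The section says that "the backwards version of the test measures working memory", but its instruction gives the patient one list to repeat both ways. There is no separate backward list in the text. Nothing in the protocol allows the effect of the forward repetition to be quantified.

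**The case against.** Section 6 leaves detailed instructions to manuals that are not shown, and 6.1.6 reads in part as a short description with example digits. The manual may already hold separate lists, more lengths and a stopping rule. The wording about continuing can loosely be read as one more step rather than an end point, and the section's reference to a backwards version may point to two administrations. This stands as a limit: the text shows what the protocol prescribes, not what sites do. It does not remove the point. Five is the only end point named, one list for both directions is the plainer reading, and a manual that differs would have to be reconciled with the protocol.

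The section also calls the test a very short screening tool, for which a narrow range may be enough. That fits poorly with its scheduled use as an efficacy measure through Month 60.

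Four stronger readings are tempting, and the documents do not support them.
- A reader might infer that backward performance below 3 cannot be recorded. A failure can be recorded; what is lost is the distinction between 0, 1 and 2.
- A reader might take the 66% to 95% who score 5 at the start as patients whose decline is invisible. Those with a true span of exactly 5 would still show a drop to 4. The cap hides a one-digit loss in 34% to 80%, on the same assumptions.
- A reader might treat the mean of 6.5 as likely. Enrolled patients are symptomatic, and the protocol gives no span data for any mean in the range.
- A reader might conclude that the cap would make decline look like stability after PR006A. Digit Span is not among the primary or secondary efficacy endpoints in 7.1.2 and 7.2.1. The study is descriptive with 15 patients, and decline is also tracked by CDR plus NACC FTLD, MoCA, Trail Making, Category Fluency, MINT and the Benson figure.

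**Conclusion.** The point holds as a minor one. Followed literally, 6.1.6 merges true spans of 5 and above, merges spans of 0 to 2, and has the backward attempt follow a forward repetition of the same digits. Its direction instruction also contradicts itself. These statements follow from the text alone.

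The size does not. The figures of -0.64 to -0.20 for a true loss of 1 digit rest on an assumed normal span, an assumed SD and mean, and an assumed longest-span score. What is affected is the sensitivity to change of one cognitive test among several. Its exact endpoint role cannot be seen, because the exploratory list is redacted. No primary or listed secondary conclusion depends on it.

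**What to change.** Reword section 6.1.6 to:
- use separate digit lists for forwards and backwards, and remove the contradictory wording on order;
- start the backward series at 2 digits;
- lengthen the series until the patient fails, rather than ending at 5;
- record the longest correct span in each direction as two scores.

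Then check the wording against the study manual that section 6 refers to, so that both give the same procedure. If the manual already does this, only the protocol text changes. Any scores already collected under the 5-digit rule should be treated as capped at 5 when change from baseline is summarised.

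The cost is an edit to one section and the rater worksheet, and slightly longer testing at each administration. Digits that were never presented cannot be recovered in the analysis, so the change is worth making early.

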### **6.1.7 Category Fluency**

The Category Fluency test involves the assessor asking the patient to name all the different examples that the patient can think of from that category in 1 minute. The categories are: animals and vegetables. The scores are summed; the higher the score, the better the category fluency.

### **6.1.8 Multilingual Naming Test**

The MINT is a 32-item test designed to assess naming skills in speakers of multiple languages ([Gollan et al 2012](#)). The 32 items are selected from a set of 68 black and white line drawings presented in order of estimated increasing difficulty.

